##### Clinical objective examination

*Myelosuppression*: There is evidence showing that cancer patients during chemotherapy often have decreased white blood cells (WBCs), hemoglobin (HGB), and platelets (PLTs) [30]. WBCs, also called leukocytes, can be divided into five types, neutrophils, basophils, eosinophils, lymphocytes, and monocytes, which are capable of defending the body against foreign invaders and infectious diseases. The WBC count is often regarded as an indicator of many diseases. During chemotherapy, the decrease of WBC counts in peripheral blood not only lead to fever, but also even septicemia and in severe cases, bleeding, which is one of the reasons for complications after chemotherapy, but these symptoms also disturb the process of chemotherapy, further reducing the efficacy of treatments [31]. HGB is an iron-containing oxygen-transport metalloprotein in the red blood cells of all vertebrates, which is essential for metabolism. Its decrease may result in anemia; the symptoms include shortness of breath, palpitation of the heart, and fatigability [32]. PLTs are derived from megakaryocytes of the bone marrow and only exist in the blood of mammals. The main function of PLTs is to stop bleeding. Chemotherapy-induced significant reduction of PLTs will cause thrombotic thrombocytopenic purpura characterized by the presence of microangiopathic hemolytic anemia, thrombocytopenic purpura, fever, renal abnormalities, and neurological abnormalities [33]. Therefore, the changes of WBC, HGB, and PLT will be assessed.

*Hepatotoxicity*: Studies showed that many patients with cancer experienced liver injury during chemotherapy [34]. From the view of Chinese medicine, the liver and kidneys are the main organs responsible for detoxification. To evaluate liver function objectively, alanine aminotransferase (ALT), aspartate transaminase (AST), total protein, and albumin (Alba) will be measured.

*Nephrotoxicity:* Liver and kidney function are important indicators in evaluating drug safety. Moreover, based on the theory of homogeny of liver and kidney in Chinese medicine, it is necessary to test kidney function. In the testing of kidney function, injury to the kidney can be exactly reflected by creatinine in the blood. The concentration change of creatinine is determined by the glomerular filtration rate, and only at a rate down to one-third of normal will the creatinine increase significantly [35]. In addition, blood urea nitrogen (BUN) is an important indication of renal (kidney) health. Therefore, creatinine (Cr) and BUN will be used as indexes to assess nephrotoxicity.

All participants will be assessed before the intervention (baseline), and 3, 6, and 12 weeks after intervention. All YH0618 materials conform to Food and Environmental Hygiene Department’s requirement for food safety and achieve the certificate of quality. The packing will be conducted at clinics of the School of Chinese Medicine, HKU. A professional research assistant will teach the subjects how to decoct the YH0618 soup, and the specific intake, water amount, and decoction time will be provided to each subject. These subjects will be asked to complete the questionnaires, undergo blood tests by themselves in hospitals, and send all testing results. Quality and compliance to intervention will be achieved by checking attendance records and the diary of self-record kept by each participant. All outcome assessors will be blinded to the intervention types of participants.

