Recent attempts to reduce toxicity by using individual compounds have been unsatisfactory [14], and there is also concern about whether using Chinese herbs will cause hepatotoxicity and nephrotoxicity or interactions with anticancer agents [15]; therefore, medical food is the best choice. YH0618, a prescription, has showed efficacy in reducing chemotherapy-induced toxicity through long clinical practice. YH0618 consists of four medical foods (such as black soybeans) which are recommended by clinicians for patients with cancer, and all components have a history of safe use in other foods. Besides, each of the components possesses a distinct pharmacological profile, including removing free radicals in the body, regulating the immune system, preventing cancer, detoxifying, and enhancing taste, etc. [16–18]. Black soybean, as the monarch drug in the prescription, has been used for detoxification over the millennia in China. Modern research has further explored its active compounds and mechanisms in detoxification. Liao et al. [19] found that a novel polysaccharide of black soybean could improve 5-flurouracil- and irradiation-induced myelosuppression in animal experiments. Anthocyanins, which are the main active compounds in the black soybean seed coat, are water-soluble and possess significant anticancer [20], antioxidation [21], liver-protective [22, 23], and kidney-protective effects [24] in vitro and in vivo experiments. Over long clinical observation, YH0618 soup has been proved to be effective in reducing chemotherapy-induced toxicity by clinical observation, but there is not yet any scientific research exploring the effects of YH0618 soup in patients with cancer. Therefore, this study will be conducted to further verify the benefits of YH0618: the hypothesis is that YH0618 soup would ameliorate chemotherapy-induced toxicity including dermatologic toxicity, hematotoxicity, hepatotoxicity, and nephrotoxicity in cancer patients who have completed chemotherapy. Moreover, since little research has explored the role of medical food intervention in reducing chemotherapy-induced toxicity, and YH0618 is a safe medical food, the project will bring huge benefits to patients with cancer. The YH0618 prescription has the potential to become a standard alternative intervention strategy in providing care to these patients.

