## Methods/design

### Study design

This is a randomized controlled trial which aims at determining whether YH0618 would be more effective than the wait-list control conditions in ameliorating chemotherapy-induced dermatologic toxicity, blood system disorders, and hepatic and renal disorders and in improving fatigue in cancer patients who have completed chemotherapy. To achieve this goal, a total of 236 patients with cancer at any stage who have completed chemotherapy within 2 weeks will be recruited for the study. The patients will be randomly divided into group A (YH0618) and group B (wait-list) using a 1:1 allocation ratio, adhering to the Consolidated Standards of Reporting Trials (CONSORT) statement [25] and the Standard Protocol Items: Recommendations for Interventional Trials (SPIRIT) statement [26]. The measures of clinical outcomes mainly include the grading of dermatologic toxicity, skin color, nail color, tongue color, and score of fatigue. Several biomarkers associated with myelosuppression, hepatotoxicity, and nephrotoxicity in the blood will also be measured. The flow chart of the study is shown in Fig. 1, and the trial process is listed in Table 1. The evaluation and data collected will be conducted at the clinics of the School of Chinese Medicine, HKU.

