**Fig. 1 Fig1:**
[figure not shown]
Flow chart of the clinical trial

**Table 1 Tab1:** Trial process chart

	Before baseline screening	Baseline	Visit 1 Treatment phase	Visit 2 Treatment phase	Visit 3 Follow-up phase
Process items		0 day	3 weeks	6 weeks	12 weeks
Patients					
Inclusion and exclusion criteria	×				
Informed consent		×			
Demographics		×			
Medical history	×	×			
Randomization and allocation concealment		×			
Primary outcomes					
Grading of dermatologic toxicity		×	×	×	×
Objective skin, nail, and tongue color (L*a*b)		×	×	×	×
Secondary outcomes					
Fatigue measurement score		×	×	×	×
Routine blood test (WBC, HGB, PLT)		×	×	×	×
Liver function (ALT, AST, total protein, Alba)		×	×	×	×
Renal function (Cr and BUN)		×	×	×	×
Adverse events			×	×	×
Patients’ diary records		Every day during the study			

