### Randomization and blinding

The research assistant will give each patient a unique study number immediately after they complete the written consent. A computer random digit (randomization list) will be generated by a statistician not involved in this study. Codes representing the two groups will be printed on one A4 opaque paper, and then be put into a envelope which is blotted out using double sided tape. The tape should be torn by the patients themselves just after completing the baseline testing. Because this trial compares the effects of the YH0618 group and the wait-list group, it is not possible to blind the patients; thus, they know which group they are in. However, the randomization sequence and different groups will be kept hidden from the practitioners, data collectors, and statisticians.

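### Blood tests are self-arranged in unspecified hospitals with no stated same-laboratory rule, so a patient who changes laboratory adds avoidable noise to the nine secondary blood outcomes

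*Protocol article*

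**What the plan says.** The hypothesis in the Background is that the soup "would ameliorate chemotherapy-induced toxicity including dermatologic toxicity, hematotoxicity, hepatotoxicity, and nephrotoxicity". The last three of those four toxicities are measured by blood tests. Table 1 lists nine measures as secondary outcomes: three for marrow (WBC, HGB, PLT), four for liver (ALT, AST, total protein, albumin) and two for kidney (creatinine, BUN). All are taken at baseline and at weeks 3, 6 and 12.

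The closing paragraph of Clinical objective examination says that participants "undergo blood tests by themselves in hospitals, and send all testing results". The same paragraph states: "All outcome assessors will be blinded to the intervention types of participants". Randomization and blinding says of the patients that "it is not possible to blind the patients; thus, they know which group they are in". Study design says: "The evaluation and data collected will be conducted at the clinics of the School of Chinese Medicine, HKU".

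Under Statistical analysis, primary and secondary outcomes at all time points go into GEE models, and the treatment effect is read from the group-by-time interaction. Missing follow-up data are to be multiply imputed. Missing values and drop-outs in the two groups are to be examined for possible bias. Covariate adjustment is planned only for variables that differ at baseline and are associated with the outcome.

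**The concern.** Laboratories can differ in calibration, method and units. If a patient's baseline sample is measured in one laboratory and the week 6 sample in another, the difference between the two enters that patient's change. Randomisation makes this noise similar in the two arms but does not take it out. The result is wider intervals for the marrow, liver and kidney parts of the hypothesis, and these nine measures are the only ones listed for those parts.

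The route by which results come back raises a second, separate matter. A patient who knows the allocation decides whether a result is sent and when the test is done. That is a question of bias, not of precision.

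**Working it through.** **The plan's own figure.** The only sample size stated is for grade 2 or higher skin toxicity: 30% versus 10%, alpha 0.05, power 90%. The two-sided pooled formula gives n = [1.96·√(2·0.2·0.8) + 1.2816·√(0.3·0.7 + 0.1·0.9)]² / 0.2² = (1.1087 + 0.7020)² / 0.04 = 81.97, hence 82 per group. With 30% attrition, 82/0.7 = 117.1, hence 118. Both stated figures are reproduced, but they concern a binary skin outcome. The article gives no SD, effect size or power for any blood outcome.

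**Count of outcomes.** 3 + 4 + 2 = 9, each measured at four visits.

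**Patient stays with one laboratory.** Let b be that laboratory's offset, additive on the scale of analysis. The change is (Y6 + b) − (Y0 + b) = Y6 − Y0, so the offset disappears. Differences between laboratories used by different patients add nothing to a within-patient change.

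**Patient switches.** With two independent laboratory offsets, the change gains a term of variance 2·(between-laboratory SD)². Let s be the between-laboratory SD divided by the SD of change within one laboratory, and q the share of patients who switch. The variance ratio is 1 + 2·q·s². The documents supply neither s nor q; both are assumptions.

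| q | s = 0.2 | s = 0.3 | s = 0.5 |
|---|---|---|---|
| 0 | 1.00 | 1.00 | 1.00 |
| 0.25 | 1.02 | 1.045 | 1.125 |
| 0.5 | 1.04 | 1.09 | 1.25 |
| 1 | 1.08 | 1.18 | 1.50 |

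The bottom row is the extreme case for each s. There the standard error grows by a factor of √1.08 = 1.04 to √1.50 = 1.22.

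**Sensitivity to the scale of s.** Suppose the between-laboratory SD is expressed instead as a fraction k of the patient SD at one visit, with correlation ρ between visits. Then s² = k²/[2(1 − ρ)]. For ρ from 0.5 to 0.8, k = 0.1 gives at most 1 + 2·0.01/0.4 = 1.05. With k = 0.5, ρ = 0.8 and every patient switching, the ratio is 1 + 2·0.25/0.4 = 2.25. The answer thus runs from nothing to large, depending wholly on quantities that the article does not report.

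**The case against.** The strongest reply is that this is an operational detail. The article condenses a full protocol that is not shown, and a same-laboratory rule may stand there. The sentence on blood tests fits equally well with each patient going to one hospital throughout. This largely stands: the article neither says nor implies that patients move between laboratories. What remains is that the procedure itself is stated (self-arranged tests, hospitals unspecified, results forwarded by the patient), and that the analysis is sensitive to the one feature the stated procedure leaves open.

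A reader might infer more from these passages. Four such readings are not supported:

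- **Tests may be done in any hospital and laboratories are mixed within patients.** The text allows this but does not say it. Mixing between patients alone costs little, because a constant offset cancels.
- **Power falls below the planned 90% with 82 per group.** Those figures belong to the skin outcome. No power was planned for a blood outcome, so none is lost.
- **Lack of blinding distorts the measured values.** Knowing the allocation does not alter an assay result. The risk lies in whether and when results are returned.
- **Study design contradicts the blood-test arrangement.** The sentence there is general, and results sent to the clinics are still collected there. It needs rewording, no more.

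On selective return, the plan does intend to examine missing values in both groups. That can detect a problem but not cure it. Multiple imputation, as usually run under missing at random, does not repair return that depends on the result itself.

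**Conclusion.** The point holds as a minor, inexpensive improvement. The stated procedure leaves it open whether a patient may change laboratory between visits, and any such change adds noise to outcomes analysed through within-patient change. Its size cannot be derived from the documents: zero if nobody switches, and an 8% to 50% rise in the variance of change if every patient switches and the between-laboratory SD is 0.2 to 0.5 of the SD of change. That calculation assumes independent offsets that are additive on the scale of analysis. The primary outcomes and the sample size are untouched. Selective return by unblinded patients is a distinct risk of bias, which the documents do not allow to be quantified.

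**What to change.** - Instruct each participant to use the same hospital laboratory for all four tests, close to the visit date, and to hand in the laboratory's own report with units and reference limits. Record any change of laboratory.
- Pre-specify the baseline value as a covariate in the analysis of each blood outcome, rather than leaving adjustment to whichever variables happen to differ at baseline. The value is already collected, and adjusting for it generally gains precision.
- Keep scaling to the laboratory's upper reference limit as a sensitivity analysis for patients who change laboratory. For a patient who stays with one laboratory with unchanged limits, it shifts the log value by a constant that cancels in the change.
- Report missing blood results by arm and visit. Handing in reports still leaves return in the patient's hands, so selective return has to be watched separately.
- Reword the sentence in Study design to say that blood tests are done in hospitals.

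The cost is one instruction to participants, a little extra data entry and one edited sentence. The downside is that some patients may be unable to return to the same laboratory; recording the switch and the sensitivity analysis deal with them. If the full protocol already holds a same-laboratory rule, the first item is met and the others remain inexpensive.

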### Adverse events

All adverse events should be reported spontaneously by patients or observed by assessors and will be recorded. Adverse events will be graded on a five-point scale (Mild, Moderate, Severe, Life threatening, Causing death). When an adverse event occurs, the investigator will take all necessary and appropriate measures to ensure the safety of the patient. Any questions concerning adverse events associated with the treatment will be reported on the study case report form and sent to the Institutional Review Board of the University of Hong Kong/Hospital Authority Hong Kong West Cluster (HKU/HA HKW IRB).

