### Ethics

Ethical approval of the study protocol was obtained from the Institutional Review Board of the University of Hong Kong/Hospital Authority Hong Kong West Cluster (HKU/HA HKW IRB, reference no. UW15-023). The trial was registered in the Chinese Clinical Trials Registry: ChiCTR-IOR-15006486. Patients will receive a detailed information sheet and complete written consent forms.

The trial is managed by the School of Chinese Medicine, HKU, and data will be supervised by the Data and Safety Monitoring Board (DSMB). Study documents (digital and hard copies) will be retained in a secure location for 5 years after trial completion.

Under the laws of Hong Kong, patients enjoy or may enjoy rights for the protection of the confidentiality of their personal data, such as those regarding the collection, custody, retention, management, control, use (including analysis or comparison), transfer in or out of Hong Kong, non-disclosure, erasure and/or any way of dealing with or disposing of any of their personal data in or for this study. Clinical trial insurance will be provided to the subjects.

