### Intervention and control conditions

Prior to intervention, baseline data will be collected including demographics, chemotherapy-induced dermatologic toxicity, skin color, nail color, tongue color, score of fatigue, and the indexes of myelosuppression, hepatotoxicity, and nephrotoxicity in the blood. After that, participants assigned to group A will receive YH0618 soup 6 days/week for 6 weeks and uncontrolled follow-up for 6 weeks, while group B are required to wait for 6 weeks and then receive YH0618 soup for 6 weeks. There is no contraindication between YH0618 soup and chemotherapy, because all the components are general food which people often eat in their daily lives.

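### Adverse-event capture relies on volunteered reports from patients who know their arm, so the weeks 0–6 comparison of symptoms not otherwise assessed is open to reporting bias

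*Protocol article*

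**What the plan says.** The Adverse events section of the protocol article gives the capture rule in one sentence: every event is to be "reported spontaneously by patients or observed by assessors", and is then recorded. It names no question to be put to the patient.

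On blinding, the Randomization and blinding section says "it is not possible to blind the patients; thus, they know which group they are in". The last paragraph of the Clinical objective examination section adds "All outcome assessors will be blinded to the intervention types of participants". On exposure, the Intervention and control conditions section says "group B are required to wait for 6 weeks and then receive YH0618 soup for 6 weeks", while group A takes the soup from the start.

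Table 1 lists adverse events at weeks 3, 6 and 12 and a daily diary, on the same schedule in both arms. The only use stated for the diary is checking quality and compliance. Blood counts and liver and kidney tests are scheduled at baseline and the same three visits, under secondary outcomes. Patients are to "undergo blood tests by themselves in hospitals, and send all testing results".

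**The concern.** Spontaneous reporting measures two things together: whether an event happened, and whether the patient thought it worth mentioning. When patients are blinded, the second part can be expected to be similar in both arms. Here it need not be. In weeks 0–6 a group A patient has a new daily intake to blame for a symptom, while a group B patient has nothing new to report on. The reverse is also plausible: a patient pleased to receive the soup may play symptoms down, and one kept waiting may complain more.

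This matters because weeks 0–6 are the only controlled safety period. After week 6 group B also takes the soup, and group A is in follow-up. The Background and Discussion already describe the soup as safe and look ahead to its use in clinical settings, so the adverse-event comparison will be read as evidence for that description.

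**Working it through.** **1. Is there a figure to reproduce?** No. The article gives no expected adverse-event rate and no reporting rate. Its only design figures are those for sample size (82 per group, 118 after 30% attrition). They reproduce with a two-sided two-proportion formula, but this point does not depend on them.

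**2. Which events depend on volunteering?**

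- Fourteen named skin, hair and nail toxicities are graded in every patient at every visit (Grading of dermatologic toxicity; Table 1). They do not depend on volunteering alone.
- Fatigue and well-being are scored by questionnaire in every patient at every visit (Fatigue measurement; Table 1). They do not depend on volunteering.
- Events visible to an assessor are recorded by someone blinded to arm, so no difference between arms is built in.
- Other symptoms that cannot be seen, such as nausea, bloating or headache, are recorded under the stated rule only if the patient raises them.

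The concern is confined to the last group.

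**3. What could differential reporting do?** Let r be the true risk of such a symptom, equal in both arms, and let c_A and c_B be the probabilities that an event is captured in each arm.

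Observed risk in an arm = r × c

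Observed risk ratio = (r × c_A) / (r × c_B) = c_A / c_B

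The true risk cancels, so the false ratio depends only on reporting behaviour. The values below are assumptions, since the article gives none. They use r = 20%.

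| c_A | c_B | Observed A | Observed B | Ratio A:B |
|---|---|---|---|---|
| 0.9 | 0.9 | 18% | 18% | 1.00 |
| 0.9 | 0.7 | 18% | 14% | 1.29 |
| 0.8 | 0.5 | 16% | 10% | 1.60 |
| 0.5 | 0.8 | 10% | 16% | 0.625 |

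With 118 per arm, the third row gives about 19 events against 12 (118 × 0.16 = 18.9; 118 × 0.10 = 11.8) when the truth is no difference. The last row can also hide harm: an assumed true ratio of 2 would appear as 2 × 0.625 = 1.25.

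**4. Laboratory results.** They are scheduled at the same visits as adverse-event recording, and all of them are sent to the study. The article does not say whether someone reviews each one for adverse-event recording, and it does not say otherwise. A comparison of means alone would be a weak check: if 3 of 118 patients (assumed) had a rise of 5 standard deviations, the arm mean would move by (3/118) × 5 = 0.127 standard deviations. That is a reason to state that results are reviewed individually. It is not evidence that they are not.

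**The case against.** The strongest objection is that this is a condensed article. Elicitation wording and adverse-event forms commonly sit in the full protocol, and Table 1 already lists adverse events at fixed visits in both arms. This does not dispose of the point, because the sentence is a positive rule covering all events and chooses spontaneous reporting. If the full protocol solicits events, the article misdescribes it and the sentence still needs changing.

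It is also fair to say that assessors are blinded, visits and diary are the same in both arms, many relevant symptoms are assessed systematically, and the Discussion admits the lack of double-blinding. All of this stands and narrows the concern to unseen symptoms outside the skin and fatigue assessments. It does not remove it: a blinded assessor cannot observe a headache nobody mentions, and the Discussion does not consider the effect on safety reporting.

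Two stronger readings are tempting and not supported.

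- **That abnormal liver, kidney or marrow results can never become adverse events.** The rule does not exclude laboratory results, and an assessor who reads a submitted result can be said to observe it. The Clinical objective examination section treats liver and kidney function as safety indicators, and the Ethics section places trial data under a Data and Safety Monitoring Board. A laboratory threshold is detail that an article may leave to the full protocol. Nor does the Background state a liver or kidney concern about this soup: its remark that "there is also concern about whether using Chinese herbs will cause hepatotoxicity and nephrotoxicity or interactions with anticancer agents" is about herbs, and it presents medical food as the alternative.
- **That the adverse-event comparison is uninterpretable, or that capture is in fact uneven.** The article establishes a risk of bias. It contains nothing on actual reporting behaviour.

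**Conclusion.** The point holds in a limited form. Unsolicited reporting by patients who know their arm leaves the weeks 0–6 comparison open to differential reporting, for symptoms other than the systematically assessed skin toxicities and fatigue. Neither size nor direction can be derived from the article. The ratios of 0.625 to 1.60 rest wholly on assumed capture probabilities and show only that the bias could create or mask a difference of practical importance. The laboratory matter is a clarification and not a defect: no safety data are shown to be lost.

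**What to change.** In the Adverse events section, replace reliance on spontaneous patient reports with one identical, non-leading question about any new or worsened problem. The blinded assessor puts it to both arms at the existing week 3, 6 and 12 visits. Keep recording anything volunteered or observed between visits, and tabulate events by arm for weeks 0–6.

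As a secondary clarification, state that scheduled results for ALT, AST, Cr, BUN, WBC, HGB and PLT are reviewed patient by patient and count as assessor-observed for adverse-event recording. The threshold for recording is for the sponsor to set.

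The cost is a change to protocol and case-report-form wording and some data entry, with no new visit or test. More minor events will be recorded in both arms. A reply may reveal the arm, so patients should be asked not to mention the soup to the assessor. An unblinded patient can still answer the same question differently by arm, so the change reduces the bias without removing it, and the trial report should say so.
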